## Abstract

**Background:**

This article describes the design of an intervention study that focuses on whether and to what degree culturally competent social robots can improve health and well-being related outcomes among older adults residing long-term care homes. The trial forms the final stage of the international, multidisciplinary CARESSES project aimed at designing, developing and evaluating culturally competent robots that can assist older people according to the culture of the individual they are supporting. The importance of cultural competence has been demonstrated in previous nursing literature to be key towards improving health outcomes among patients.

**Method:**

This study employed a mixed-method, single-blind, parallel-group controlled before-and-after experimental trial design that took place in England and Japan. It aimed to recruit 45 residents of long-term care homes aged ≥65 years, possess sufficient cognitive and physical health and who self-identify with the English, Indian or Japanese culture (*n* = 15 each). Participants were allocated to either the experimental group, control group 1 or control group 2 (all n = 15). Those allocated to the experimental group or control group 1 received a Pepper robot programmed with the CARESSES culturally competent artificial intelligence (experimental group) or a limited version of this software (control group 1) for 18 h across 2 weeks. Participants in control group 2 did not receive a robot and continued to receive care as usual. Participants could also nominate their informal carer(s) to participate. Quantitative data collection occurred at baseline, after 1 week of use, and after 2 weeks of use with the latter time-point also including qualitative semi-structured interviews that explored their experience and perceptions further. Quantitative outcomes of interest included perceptions of robotic cultural competence, health-related quality of life, loneliness, user satisfaction, attitudes towards robots and caregiver burden.

**Discussion:**

This trial adds to the current preliminary and limited pool of evidence regarding the benefits of socially assistive robots for older adults which to date indicates considerable potential for improving outcomes. It is the first to assess whether and to what extent cultural competence carries importance in generating improvements to well-being.

**Trial registration:**

Name of the registry: ClinicalTrials.gov

Trial registration number: NCT03756194.

Date of registration: 28 November 2018. URL of trial registry record.

## Contributions to the literature

The CARESSES trial is one of the largest studies into the effectiveness of socially assistive robots (SARs) in improving health-related outcomes for older adults to date. The trial builds on the existing limited but promising evidence-base.The trial explores the impact of cultural competence by exploring if and how SARs employing the CARESSES culturally competent artificial intelligence produce improvements in outcomes.The complex and ethically sensitive methodology will aid future studies aiming to evaluate the impact of SARs on health-related outcomes.The results will aid the development of policies on the use of artificial intelligence and robotics in such settings.

## Background

CARESSES (Culture-Aware Robots and Environmental Sensor Systems for Elderly Support) is a multidisciplinary, international project whose goal is to design, test and evaluate socially assistive robots (SARs) configured to assist older adults residing in long-term care homes in a culturally competent manner [1].

Culturally competent robots autonomously re-configure their way of interacting with a user in a way that is appropriate to the culture, customs, and preferences of the person they are assisting. They begin by understanding which culture, at a group-level, the user primarily identifies with and as such accesses a relevant cultural knowledge database. The robot uses this database (a hierarchically structured ontology employing causal Bayesian networks that express correlations between different concepts) as a basis of its verbal and non-verbal interactions but then adapts its understanding of the user’s individual preferences and values as it receives feedback from the user during an interaction [2]. For example, the robot may initially guess that an American individual values baseball and not rugby and thus offers to talk about baseball. However, if the user expresses their dislike for baseball and a preference for rugby, then the robot’s understanding will change accordingly and, during subsequent interactions, will be more likely to initiate conversations about rugby than previously. By leveraging the principles of cultural competence during interaction with users, it is hypothesised that users may be more likely to accept and value interactions with SARs compared to SARs that do not perform this. This is important given how critical user acceptance is for the successful implementation of any public health intervention [3].

Cultural competence is also a concept that is linked to improved health outcomes among patients particularly within the nursing literature [4–7]. Papadopoulos [4] defines cultural competency as the ability to respond effectively to people from different cultures and backgrounds that can subsequently assist healthcare professionals in the delivery of services that meet the cultural and communication needs of patients. This concept has never previously been implemented and evaluated within robotics despite its importance for enhancing patient-centred care.

The evidence to date regarding the effectiveness of SARs in improving health-related outcomes for older adults is promising. For example, Abdi et al’s [8] scoping review of 33 studies consisting of 1574 participants and 11 robots showed that 28 of the 33 papers reported positive outcomes (five studies showed non-significant findings), and that SARs could be employed to offer a wide range of roles within the elderly care context particularly cognitive training, social facilitation, and companionship, for which findings were consistently positive. The authors also found SARs could also be useful in providing physiological therapy and affective therapy. However, for the latter, the findings were not clearly better than a comparative soft-toy or placebo robot, while for physiological therapy the results were sometimes clinically unpredictable. They conclude that the potential for SARs for improving outcomes is promising but that further evidence is required. A systematic review and meta-analysis of the effectiveness of SARs for older adults by Pu et al. [9] made similar conclusions. Their review synthesised evidence from 11 randomised controlled trials of SAR interventions for older adults, observing that SARs produced positive impact on agitation, anxiety, and quality of life for older adults, as well as indications that social robot interactions could improve engagement, interaction, and reduce loneliness. Due to such observations as well as concerns over study quality, the authors conclude that “the potential for social robots to improve cognition, depression, and apathy needs further investigation” (p13).

The CARESSES study is formed on the points and issues highlighted above, namely that it is reasonable to expect that leveraging cultural competence within socially assistive robots may yield particularly positive improvements in user outcomes and acceptance, and that there is a clear need for further research of SARs within the context of supporting older adult care. The need for effective, safe and acceptable interventions is underlined by the aging populations across the world. For example, it is estimated that by 2030, approximately one in five people in developed countries will be aged over 65 years, and that the population of over 85 years olds will almost triple by 2050 [10]. Such demographic changes are putting increasing pressure on health and social care systems especially regarding employee turnover and shortages [11]. In the UK alone, it is anticipated that over two million new workers will need to be trained and recruited into the health and social care sector between 2012 and 2022 [12].

The CARESSES project began in January 2017 and consists of a range of different work packages led by different research partners across Europe and Japan. The current protocol only describes the procedures used for testing work package (that was completed in November 2019) and also the evaluation work package (due to be completed in early 2020). The overall aim of these work packages are to conduct and evaluate a controlled before and after experimental trial aimed at exploring if and to what extent SARs employing the CARESSES culturally competent artificial intelligence can produce better health and well-being related outcomes among older adults residing in long stay care homes (as well as their informal carers) compared to a control robot, and care as usual (no robot intervention). The control robot possesses all of the same functionalities of the CARESSES robot but employs cultural competence in what the study team believe to be a less valid and reliable way. The specific objectives are:
Whether and to what degree improvement in health and well-being related outcomes are observed among participants in the experimental group, compared to those in the control groups.Whether and to what degree the CARESSES robot was assessed by participants as more culturally competent than the CARESSES control robot.To investigate participants’ views of the CARESSES robot’s cultural competence, including how and why they think the robot impacted their well-being, and whether and why they accepted the robot and its assistance.To assess cost-effectiveness of the intervention compared to costs of care alternatives

## Methods

### Study design

A mixed-method, single-blind, parallel-group controlled before-and-after experimental trial with 1:1 participant allocation was employed between March and November 2019 within eligible long-term older adult care homes in England and Japan. The care homes were predominantly those owned by Advinia Health Care (a full research partner in the project) from which English and Indian residents were recruited, and also within the HISUISUI assisted living facility in Japan from which Japanese residents were recruited. The testing procedures took place within participants’ bedrooms only. A pre-trial pilot study was successfully employed in November and December 2018 in one UK-based care home that assessed the feasibility, acceptability and fidelity of the intervention and its procedures. This led to a range of procedural and technical improvements made prior to the commencement of the full trial.

### Participants

A total number of 45 residents of older adult long-term care homes, who self-identify themselves as primarily belonging to English (*N* = 15), Indian (N = 15) or Japanese (N = 15) cultures were aimed to be recruited within the UK (*N* = 30) and Japan (N = 15). The other eligibility criteria for participating residents were:
Aged ≥65 years.Resided in a single occupancy bedroom / bedroom area.Unlikely to express aggression towards themselves, the robot, and/or the researcher.Possessed sufficient cognitive competence.Possessed sufficient physical health.Able to verbally communicate in English (UK site only) or Japanese (Japan site only).

To determine residents’ eligibility, a two-staged screening procedure was employed. During the first stage, care home staff nominated residents (using initials only to protect anonymity) who they believed met the inclusion criteria. Only staff who directly provided care to the residents and therefore possessed knowledge of each residents’ physical and cognitive competency were requested to make these nominations. During the second stage, the research team supported the nominating care home staff in using the following screening tools which establish participant eligibility. For assessing cognitive competence and aggressiveness, the interRAI-Long Term Care Facility ‘Cognitive Performance Scale’ and Aggressive Behaviour Scale’ sub-scales were used [13]. For the cognitive scale, scores range from 0 (intact) to 6 (very severe impairment), with a score of 3 or more indicating moderate to severe impairment. Therefore, given the need for reasonable cognitive understanding of how to use and interact with the robot, a threshold of ≤2 was set. For the aggression scale, a total score above 0 indicates a reasonable likelihood of aggression and therefore, to reduce this risk, a threshold of < 1 was set. For assessing frailty (a proxy to physical health), the FRAIL-NH scale [14] was employed with an applied threshold of ≤10. This has previously been recommended as a cut-off for grouping higher/lower frailty in the older adult population residing in long-term care home settings [15]. Residents who passed the second screening stage were then approached, with a researcher being introduced to the resident by a care home staff member at a convenient and appropriate time. Residents were not asked to consent to being nominated or screened during these stages because there was a reasonable likelihood that doing so could have caused confusion and upset to some residents. For example, the researcher may have caused a resident confusion and potentially distress had the resident misunderstood our request because of poor cognitive competence. Further, if a resident provided consent and was keen to participate but was subsequently not invited, it may have caused disappointment.

Approached residents were then provided a participant information document and informed consent document (produced following Care Quality Commission and Alzheimer Europe Ethical Guidelines recommendations) as well as a study leaflet that visually informed residents of the hardware and outlines some of its functionalities. The researcher then offered to read these documents aloud to the resident and encouraged him/her to speak with informal carers if they were interested in participating. If a resident wished to provide consent but could only do so through verbal means, then this was conducted in the presence of a literate witness who could countersign the consent document on behalf of the participant. A rolling consent approach was also adopted throughout the study to help ensure that participants may withdraw at any time. To incentivise participation, residents were offered a £30/¥4000 voucher if they were allocated to the care as usual group. Participants who received a robot were also provided with a printed photo album and videos of their time with the robot after their final testing period had been completed.

Residents who provided consent were asked to nominate up to three informal carers to participate and, if multiple informal carers were nominated, to indicate who they considered to be their primary informal carer. A researcher then contacted the primary informal carer (if applicable) to invite them to also participate. If he/she declined, another nominated informal carer was contacted and invited to participate. If three informal carers were nominated, the process would be repeated a final time if the second informal carer also declined. When a meeting to seek their consent to participate was arranged (which took place at a mutually convenient time either in-person or via a phone call or videoconferencing), a researcher provided the informal carer with a study leaflet, a participant information document and informed consent form (all tailored for their use). To incentivise participation, informal carers were offered a £30/¥4000 voucher.

Beyond being nominated, informal carers were eligible to participate if they met the following additional eligibility criteria:
Aged ≥18 years.Had visited the participant in the care home within the past 3 months.Provided any type of informal help, care and/or support to the participant.Were a relative, partner, friend or neighbour who has a significant personal relationship with the participant.Were not paid or officially employed to provide care to the participant.Able to communicate in English (UK site only) or Japanese (Japan site only).

Due to financial, time and resource restrictions (UK: 20 weeks for testing procedures, two robots only; Japan: 12 weeks for testing procedures, three robots only), and the inability to statistically power this intervention (due to the novelty of the intervention and thus uncertainty over what might constitute a clinically meaningful difference in outcomes), it was unlikely to be possible to collect data from more than 15 participating care home residents per cultural group. See Fig. 1 and Table 1 for a breakdown of the recruitment procedure and study design.

**Fig. 1 Fig1:**
[figure not shown]
Study design flow chart

**Table 1 Tab1:** Study design overview

	English group	Indian group	Japanese group
**N participants (residents) total**	15	15	15
**N participants (informal carers) total**	15	15	15
**Testing site**	England	England	Japan
**Participant and intervention language used**	English	English	Japanese
**N participants (residents + informal carers) in experimental group**	5 + 5	5 + 5	5 + 5
**N participants (residents + informal carers) in control group 1**	5 + 5	5 + 5	5 + 5
**N participants (residents + informal carers) in control group 2**	5 + 5	5 + 5	5 + 5
**Duration of robot interaction testing period (for residents in experimental or control group 1)**	2 weeks: • Week 1: 3 days, 45 min - 3 h per day (rotated). First session is training, all other sessions independent use with standby support ready. • Week 2: 3 days, 45 min - 3 h per day (rotated) – Independent use with standby support ready.		
**Total time required for testing**	20 weeks		12 weeks

### Allocation and blinding

Participants were allocated to one of three study groups using random sampling stratified by gender. The study groups were as follows: experimental group (utilizing a CARESSES experimental robot), control group 1 (utilizing a CARESSES control robot) and control group 2 (care as usual without robot intervention). Participants (both residents and their informal carers) who received a robot were blinded to which type of robot they received (the experimental or control robot). Care home staff were also blinded and there were no circumstances under which unblinding was permissible.

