#### Boosting standardisation between sites

To boost standardisation of procedures between the UK and Japan based sites, a number of procedures took place. First, a highly detailed protocol had been produced between the lead partners of both sites. In addition, to aid the development of the protocol, informal visits of candidate care homes in different sites had been made by the lead partners of both sites. Third, pre-existing validated Japanese translations of research instruments had been selected where possible, with all other relevant documents undergoing professional translation. Fourth, researchers from both sites had undergone the same ethics and methods training procedures and took part in a number of additional preparatory meetings, both in person (during yearly pre-planned project meetings) and online using Zoom videoconferencing software. Fifth, the Japanese procedures commenced 3 months after the commencement of procedures in the UK. This helped to ensure that any unanticipated required procedural changes could be considered and planned for prior to Japanese testing. Finally, step-by-step manuals to aid implementation of technical and methodological procedures between sites had also been produced.

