### Data analysis

This work underpins the evaluation work package of the CARESSES study which shall be completed in early 2020. Quantitative data will be analysed using the IBM SPSS statistical software version 21.0 [22]. Kolmogorov-Smirnov tests will be initially conducted to establish the normality of the dependent variables. As appropriate, independent samples t-tests (for normal distribution), Mann-Whitney U tests (for non-normal distribution), or Chi-Square tests (normal or non-normal) will be used to compare the independent and dependent variables between the two groups/arms, in addition to simple descriptive statistics (means, medians and SDs as appropriate). For within-group repeated analyses, dependent t-tests (for normal distribution) and Wilcoxon signed-rank tests (for non-normal distribution) will be used to assess changes between pre-test and post-test scores. The level of statistical significance will be set at *p* ≤ 0.05. Linear mixed models will be used to assess the magnitude of differences in changes between the experimental and control groups. Drop out and intention-to-treat analyses will also be conducted. Fidelity will be assessed through a fidelity implementation checklist to be completed by the research team as the procedures take place. To assess cost-effectiveness, the EU MAFEIP (Monitoring and Assessment Framework for the EIP on Active and Healthy Ageing) tool will be used to estimate lifetime incremental quality-adjusted life years (using SF-36 data) with incremental cost of our intervention (compared against costs of care alternatives).

Qualitative data will be transcribed verbatim, entered into NVivo software Version 10.0 [23] and analysed using thematic analysis as described by Braun and Clarke [24]. This will involve two researchers independently reading and re-reading the transcripts to familiarize themselves with the data and independently labelling the data into categories and codes. Meaningful patterns across all the codes that are identified will be sorted into themes. All the codes under each theme will then be reviewed to confirm the validity of each theme and to produce overarching themes.

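### Allocation is described as stratified by gender only, which would rarely give Table 1's 5 residents per arm in each culture, and the named between-arm tests adjust for neither culture nor gender

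*Protocol article*

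**What the plan says.** The section Allocation and blinding gives the whole allocation rule in one sentence: "Participants were allocated to one of three study groups using random sampling stratified by gender". Blocks, culture and site are not mentioned there. Study design describes a "parallel-group controlled before-and-after experimental trial with 1:1 participant allocation".

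Three places give numbers. The abstract sets 15 residents in each of the three arms. Participants sets 15 per culture as a recruitment target. Table 1 crosses the two: the row "N participants (residents + informal carers) in experimental group" reads 5 + 5 under English, Indian and Japanese alike, and the rows for the two control groups read the same.

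On timing, Boosting standardisation between sites says that "the Japanese procedures commenced 3 months after the commencement of procedures in the UK", which left room for procedural changes before testing began in Japan.

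Data analysis names t-tests, Mann-Whitney tests and chi-square tests, which "will be used to compare the independent and dependent variables between the two groups/arms". It then adds: "Linear mixed models will be used to assess the magnitude of differences in changes between the experimental and control groups". No covariate is listed for any of these analyses.

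**The concern.** The one stratification factor that the article declares does not produce the layout in its own design table. Balancing gender across arms does nothing to hold each culture at 5/5/5.

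Culture is not an incidental variable here. The experimental robot loads a culture-specific knowledge base and the control robot a generic one, so culture is the trial's central grouping. It also coincides with country, with interview language and, for Japan, with translated instruments and the later start. The outcomes are self-report scales, on which groups that differ in these ways may well score differently. With 15 residents per arm, a few more Japanese residents in one arm than another can move an arm mean for reasons unrelated to the robot.

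The named two-sample tests carry no covariates. They therefore ignore both the declared stratifier and the grouping around which recruitment was organised.

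**Working it through.** **Inputs from the article.** Three arms of 15 (abstract); three cultures of 15 (Participants); 5 per arm-by-culture cell (Table 1); gender as the only stratifier (Allocation and blinding); significance at 0.05 (Data analysis; taken as two-sided). The gender split within culture and the size of any culture effect are not given, so both are assumptions below.

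**Table 1 reproduced.** 3 arms × 3 cultures × 5 = 45 residents, 15 per arm and 15 per culture. The totals agree, and 5 is the expected cell count under any 1:1:1 allocation. The question is how often all nine cells equal 5.

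**One list pooled over cultures, arms held at 15.**
- Ways to split one culture 5/5/5: 15!/(5!)³ = 756,756.
- P(all nine cells = 5) = 756,756³ / [45!/(15!)³] = 4.334 × 10¹⁷ / 5.349 × 10¹⁹ = 0.0081, or 0.8%.
- With gender strata added (simulation, 50,000 runs for each of five assumed splits, 8 to 12 women of 15 per culture): 0.70% to 0.80%. Stratifying by gender leaves the figure almost unchanged.
- At least one cell with 3 or fewer residents: about 77% (76.4% by exact enumeration ignoring gender). With 2 or fewer: about 31%.

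**One list for the UK, a separate one for Japan.** P(English and Indian both 5/5/5) = 756,756² / [30!/(10!)³] = 5.727 × 10¹¹ / 5.551 × 10¹² = 0.103, or about 10%, ignoring gender.

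**A list within each culture.** A list fixed at 5/5/5 delivers Table 1 with certainty. Gender blocks of 3 inside each culture do so only when the gender counts are multiples of 3; otherwise the chance is about 34% per culture. Blocks of 6 give about 26% to 40%.

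**What an imbalance could do.** Take the number of Japanese residents in the experimental arm minus the number in control group 1, on the pooled list. Its variance is 2 × 15 × (1/3)(2/3) × (30/44) + 2 × 15² × (1/3)(2/3)/44 = 4.55 + 2.27 = 6.82. The SD is 2.61 residents, and 2.61/15 = 0.17 of an arm. If Japanese scores differed from the others by 1 SD (assumption), the arm contrast would shift by chance with a standard deviation of about 0.17 SD. The Japanese share differs by 20 percentage points or more in 34% of allocations.

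**Type I error of the unadjusted t-test, 15 versus 15** (10,000 runs per case, one culture shifted by an assumed amount):

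| Culture shift | Culture not balanced | 5/5/5 forced |
|---|---|---|
| 0.5 SD | 5.0% | 4.4% |
| 1.0 SD | 5.1% | 3.3% |
| 1.5 SD | 5.1% | 1.5% |

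Averaged over random allocations the test keeps its level. Under forced balance it is conservative, because between-culture variance stays in the error term although balance has removed it from the contrast.

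**Precision from adjusting.** The gain is roughly 1/(1 − R²), where R² is the share of outcome variance due to culture. For an assumed R² of 0.10 to 0.30 this is 1/0.90 = 1.11 to 1/0.70 = 1.43. The documents give no R².

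**The case against.** The strongest reply is that the two statements are compatible. The low probabilities need a list pooled over cultures or over the UK, and the article does not say there was one. Separate sites, a target of 15 per culture and a staggered start make lists run within culture plausible, and gender stratification inside each culture could fit Table 1. The table is also a design overview of target numbers. This stands in part: the article does not rule out allocation within culture, but it does not state it either. A separate Japanese list alone would not settle the English and Indian split.

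A reader might infer that culture confounds the arm contrasts. The documents do not support that. Allocation is described as random, so any imbalance is chance, and the table above shows the unconditional error rate staying near 5%.

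A reader might also infer that no analysis adjusts for culture or gender. That is established only for the t-test, Mann-Whitney and chi-square tests. The covariates of the mixed model are not listed and may be given in a fuller protocol or analysis plan that is not shown.

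Two further points stand. The mixed model works on changes, and the SF-36, the loneliness scale, the robot attitudes scale and the carer burden inventory are all taken at baseline and at 2 weeks, so stable differences in level between cultures largely cancel. That protection is missing for CCATool-Robotics, collected at weeks 1 and 2, and for QUIS, collected at week 2 only. Finally, testing ended in November 2019, so the allocation list can no longer be changed.

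**Conclusion.** The concern holds as a mismatch to reconcile and an avoidable weakness in the analysis. The stated rule would give Table 1 in about 0.8% of allocations on a pooled list, and the UK part of it in about 10% on a UK list. Allocation within culture would explain the table, but no section describes it.

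The two harms belong to alternative scenarios and do not add up. If culture was not a stratum, chance imbalance goes uncorrected in the named tests. If 5/5/5 was forced, those tests are conservative, with type I error of about 4.4% down to 1.5% for shifts of 0.5 to 1.5 SD. Adjusting for culture and gender answers both. The concern is greatest for CCATool-Robotics and QUIS, which have no baseline.

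The allocation probabilities follow from the article's own counts and depend little on the gender split. The size of the harm and of the precision gain rests on assumed culture effects. Severity is moderate: the article says that the trial is not powered and that its results are preliminary.

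**What to change.** 1. Reconcile Allocation and blinding with Table 1 by stating the allocation actually used. If culture was a stratum, name it and say how 5/5/5 was obtained. If it was not, label Table 1 as target numbers and report the achieved count in each of the nine cells.
2. Base the between-arm contrasts on models with culture (3 levels) and gender as fixed effects, in place of the unadjusted t-test or Mann-Whitney test. State these two terms for the linear mixed model as well. CCATool-Robotics and QUIS need this most.

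The cost is 3 degrees of freedom (2 for culture, 1 for gender) and a few sentences. Both variables are already known for every resident, and the article describes the analysis as still to come. Nothing in the conduct of the trial has to change.
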